##### 4.3 Exclusion criteria

None.

##### 4.4 Sample size calculation

A power calculation beforehand is not possible because it is unknown how many and which methylation profiles will be identified. However, based on previous experiments to generate reference profiles using MeD-seq, the number of reliable DMRs stabilizes with a sample size of minimal 10 individuals as a consequence of filtering out SNPs and other genomic variation that in <10 samples might still be picked up as DMR. Therefore, in this

pilot study we include twenty patients per group, ten as training dataset and 10 patients for internal validation.

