## PROTOCOL SUMMARY

DNA methylation plays a vital role in placental development and methylation differences are associated with multiple placental related complications. Placental-originated cell free DNA (cfDNA) circulates in maternal plasma, providing the opportunity to non-invasively study placental DNA methylation during pregnancy. Up until recently, cfDNA was already widely used for non-invasive prenatal testing (NIPT) on a trial base (TRIDENT-2 study) and cfDNA screening is currently implemented in regular health care.

We aim to identify differentially methylated regions (DMRs) in cfDNA from residual NIPT samples between women who at a later gestational age developed preeclampsia (group 1), intrauterine fetal growth restriction (group 2) and spontaneous preterm birth (group 3) all as compared to uncomplicated pregnancies (group 4). Included women who delivered at the Erasmus MC and/or participated in The Rotterdam Periconception Cohort (PREDICT study, MEC-2004-227) will retrospectively be selected..

We will use the Methylated DNA sequencing (MeD-seq) technology to identify DMRs genome-wide. MeD-seq requires a limited amount of input DNA and is therefore compatible with the low levels of cfDNA available in clinical practice. Based on previous experiments to generate reference profiles using MeD-seq, the number of identified DMRs stabilizes when having samples from ten different individuals. Therefore, to prevent the identification of unreliable DMRs (related to genomic variation), we intend to include twenty patients per group (training and validation set), with a total of four groups in this pilot study.

Since suboptimal implantation and placentation in the beginning of pregnancy is involved in the pathophysiology of placental related complications, we hypothesize to identify disease-specific DMRs already present at the end of first trimester. NIPT sampling is usually performed between 11 and 13 weeks of gestation. Identified DMRs can potentially serve as biomarkers able to predict disease risk.

Second, we aim to identify underlying genes or genetic pathways related to identified DMRs involved in disease development, improving our understanding of underlying pathophysiology. This study could potentially lead to an expansion of current NIPT (Epi-NIPT), and initially will serve as a validation cohort for future studies into cfDNA.

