#### 4. Study population

##### 4.1 Population (base)

Eligible women participated in the TRIDENT-2 study and during the same pregnancy participated in the Predict study and/or delivered at the Erasmus MC Rotterdam.

Women who developed preeclampsia, intrauterine growth restriction or spontaneous preterm birth will be included and compared to controls with an uncomplicated pregnancy. We aim to include samples from twenty women per group (total n=80).

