## 5. Methods

### 5.1 *Please describe how you do conduct research and which methods are used, e.g. questionnaires, human material collection, extraction of data from medical records, analysis of images, the use of an app/medical device/diagnostic test, clinical tests to be performed, etc. Include information on frequency, duration, volumes, if a Data Management Plan is available (then please upload DMP).*

This study will use data previously collected in the Predict study, medical records, and blood samples previously collected for NIPT in the TRIDENT-2 study. Participation in the TRIDENT-2 study will be checked for Predict participants and for eligible patients who had complicated deliveries at the Erasmus MC Rotterdam in the last two years in collaboration with the Clinical Genetics Department at the Erasmus MC. Cases and controls will be selected until twenty patients in each group are selected. The MeD-seq technology will be used to investigate DNA methylation profiles in cfDNA between women who developed preeclampsia, intrauterine growth restriction or spontaneous preterm birth compared to uncomplicated control pregnancies. Custom Python scripts will be used to process the acquired DNA methylation profiles. Raw data files (fastq) will be filtered to be able to distinguish methylation data from background data and will be mapped to the human genome (hg38) using bowtie. To subsequently analyse DMRs, we will generate both regional (promoter, gene body and CpG Island regions) as genome-wide methylation scores. For the genome wide analysis, a sliding window technique will be used to detect DMRs. The Chi-squared test will be used for statistical testing with either the False Discovery Rate (FDR) or Bonferroni correction for multiple testing. A FDR or Bonferroni adjusted p-value <0.05 will be considered significant. After DMRs are determined, Z-score transformation of the read count data will be applied for unsupervised hierarchical clustering analysis. Pathway analyses will be performed using <http://geneontology.org>.

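### Sub-study 3 relies on ten women per set to filter out SNPs; that size thins out rare variants but leaves common ones, some of which can be called as DMRs

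*Protocol*

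**What the plan says.** In sub-study 3, Section 4.4 declines a power calculation and rests the group size on earlier MeD-seq reference-profile work. There the number of reliable DMRs "stabilizes with a sample size of minimal 10 individuals as a consequence of filtering out SNPs and other genomic variation", variation "that in <10 samples might still be picked up as DMR". The design follows from this: "pilot study we include twenty patients per group, ten as training dataset and 10 patients for internal validation". The Protocol Summary gives the same purpose: "to prevent the identification of unreliable DMRs (related to genomic variation), we intend to include twenty patients per group".

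Section 5.1 describes one filter on the sequence data: "Raw data files (fastq) will be filtered to be able to distinguish methylation data from background data". On testing it says: "The Chi-squared test will be used for statistical testing with either the False Discovery Rate (FDR) or Bonferroni correction for multiple testing". The threshold is: "A FDR or Bonferroni adjusted p-value <0.05 will be considered significant". It does not say whether the chi-squared test counts reads pooled over a group or treats each woman as a unit. Section 4.3 lists no exclusions, and Section 5.1 selects cases and controls until each group is full. No balancing on ancestry is mentioned.

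**The concern.** The protocol itself names SNPs as a source of false DMRs and gives sample size as the remedy. MeD-seq relies on a methylation-dependent restriction enzyme, as the title of its cited method paper says. An allele that destroys the recognition site therefore removes reads just as lost methylation would. Averaging over ten women makes a rare private variant unimportant. A common variant is carried by several women in each group, and its frequency still differs between small groups by chance.

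The main endpoint is disease-specific DMRs, and the summary proposes them as possible biomarkers. A genotype difference that passes as a DMR would enter that list. The expected signal is also small. The introduction to sub-study 2 puts the placental share of maternal cfDNA at 13% on average, so even a 100-point methylation difference in placenta moves total cfDNA by about 1.00 × 13 = 13 points. Chance genotype differences at n=10 are of that size, as shown next.

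**Working it through.** **The plan's figure.** Only the multiplication can be reproduced: 10 training + 10 validation = 20 per group, and 4 × 20 = 80. The ten itself comes with no formula, allele frequency, read depth or data. Addendum 3 puts the same stabilisation at about 8–9 samples.

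**Step 1: chance genotype differences (exact).** Let p be the minor allele frequency. With n women per group, each group's allele count is Binomial(2n, p), and the SD of the difference in frequency is √(2p(1−p)/2n). At n=10, a gap of at least 20 points means a difference of at least 4 alleles out of 20.

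| p | SD of difference, n=10 | P(gap ≥ 20 points) |
|---|---|---|
| 0.2 | 0.126 | 16% |
| 0.3 | 0.145 | 23% |
| 0.5 | 0.158 | 27% |

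Nothing changes sharply at ten. At p=0.3 the SD is √(0.42/18) = 0.153 with nine women and √(0.42/20) = 0.145 with ten.

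**Step 2: what a test on pooled reads makes of this.** Assume one read-out site fully dependent on the SNP, Poisson reads proportional to intact alleles, d reads per woman when both alleles are intact, and no disease effect. Per woman, the mean count is d(1−p) and the between-woman variance is d²p(1−p)/2. The variance-to-mean ratio is then 1 + dp/2, while the pooled test assumes 1. At d=30 and p=0.5 the ratio is 1 + 7.5 = 8.5. The cut-off for two-sided 1e-6 is z = 4.89, and it behaves like 4.89/√8.5 = 1.68, a tail of about 9%. At p=0.2 the ratio is 4 and the cut-off behaves like 4.89/2 = 2.45, a tail of about 1.4%. The ratio does not contain n, so adding women does not lower the rate. At d=20 and p=0.5, simulation gives 4.9%, 4.7% and 4.6% at n = 5, 10 and 50.

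**Step 3: simulation, ten against ten, p from 0.2 to 0.5.** Training needs p<1e-6. Validation needs the same direction and p<0.05 in a fresh ten against ten. The documents give neither depth nor the number of tests, so both depth and threshold are assumptions.

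| Reads per woman | Called in training | Also passes validation |
|---|---|---|
| 5 | 0.005%–0.08% | below 0.01% |
| 10 | 0.06%–0.9% | 0.005%–0.13% |
| 30 | 1.6%–10% | 0.3%–2.5% |
| 100 | 14%–34% | 4%–12% |

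The nominal training rate is 0.0001%. If validation must also reach 1e-6, the 30-read figure falls to about 0.01%–0.5%.

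**Step 4: conditions that shrink the rate.** With five equal sites in a region, one of them carrying the SNP, the training rate is about 0.006%–0.03% at 30 reads and 0.3% to a little over 1% at 100 reads. With alleles as the unit, standing for a test that respects women as units, the exact rate at 1e-6 is between 4e-9 and 2.4e-7, so practically no SNP is called.

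**Step 5: unequal ancestry.** With assumed frequencies of 0.20 and 0.35 in the two groups, a 20-point gap occurs in 44% of comparisons at n=10. Under pooled reads, about 6% of such sites pass both sets at 30 reads and 14% at 50. At 30 reads the 6% rises to about 14% with 20 women per set and 44% with 50, because here the frequency difference is real.

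**The case against.** Much can be said on the other side, and most of it limits the point.

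- **Group size is not the only safeguard.** A reader might infer that it is. Section 4.4 also sets aside ten women per group for validation, and chance imbalance in one set is independent of that in the other. At 30 reads, validation removes roughly three quarters or more of the false calls (10% to 2.5%; 1.6% to 0.3%). It does not remove them all.
- **The calls are conditional.** A reader might infer that common SNPs will be reported as disease DMRs. That needs pooled reads, ample depth and little dilution by neighbouring sites. The protocol states none of these, and its endpoint is regions and windows.
- **The number ten is not the cause of the false calls.** Under pooled reads the rate hardly depends on n; the unit of the test drives it. This stands, and it also shows that group size cannot do the job the protocol assigns to it.
- **A variant mask may be in an analysis plan that is not shown.** Its absence is therefore not the finding. The finding is the protocol's statement that ten individuals do the filtering.
- **The earlier experiments are unseen.** The calculation does not show that DMR counts failed to stabilise. It shows that stabilisation at ten cannot be credited with removing common SNPs.
- **Sub-study 2 is outside the point.** A reader might extend it there, because its Section 4.4 also cites ten samples. That text mentions neither SNPs nor genomic variation, so the extension is not supported.

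**Conclusion.** The point holds in limited form. Ten women per set reduce rare or private variants but do not by themselves remove common SNPs, contrary to Section 4.4 and the Protocol Summary of sub-study 3. The 16%, 23% and 27% figures are exact and assume only random sampling of alleles from one population.

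The rate of false DMRs depends on unstated choices. For single-site SNPs under pooled reads, from 0.005%–0.13% (10 reads) to 4%–12% (100 reads) would survive both sets. It is far lower in multi-site regions and practically nil with women as the unit. The number of affected sites is not given, so no total can be stated. Ancestry imbalance is the case that validation covers least, since both sets come from the same groups. The documents give no ancestry data, so the 0.20 against 0.35 example is illustrative only.

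**What to change.** In Section 5.1 of sub-study 3, add a step before DMR calling that masks MeD-seq read-out sites overlapping common variants in a public variant database (for example minor allele frequency of 1% or more). Recompute the regional and sliding-window scores without those sites.

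In Section 4.4 and the Protocol Summary, restate the rationale: ten individuals per set reduce the influence of rare or private variants but do not by themselves remove common SNPs.

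The mask is a bioinformatic step on data already planned and needs no new samples. Its cost is the loss of a small share of CpG sites. No change to sub-study 2 is asked for on this ground.

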#### 4.5 (Planned) start date

We plan to start the collection of additional residual NIPT samples right after METC approval.

#### 4.6 (Planned) end date

Sequencing of samples and data-analysis are performed in the following six months.

## 5. Methods

### 5.1 *Please describe how you do conduct research and which methods are used, e.g. questionnaires, human material collection, extraction of data from medical records, analysis of images, the use of an app/medical device/diagnostic test, clinical tests to be performed, etc. Include information on frequency, duration, volumes, if a Data Management Plan is available (then please upload DMP).*

This study will use data previously collected in the Predict study, medical records, and blood samples previously collected for NIPT in the TRIDENT-2 study. Participation in the TRIDENT-2 study will be checked for Predict participants and for eligible patients who had complicated deliveries at the Erasmus MC Rotterdam in the last two years in collaboration with the Clinical Genetics Department at the Erasmus MC. Cases and controls will be selected until twenty patients in each group are selected. The MeD-seq technology will be used to investigate DNA methylation profiles in cfDNA between women who developed preeclampsia, intrauterine growth restriction or spontaneous preterm birth compared to uncomplicated control pregnancies. Custom Python scripts will be used to process the acquired DNA methylation profiles. Raw data files (fastq) will be filtered to be able to distinguish methylation data from background data and will be mapped to the human genome (hg38) using bowtie. To subsequently analyse DMRs, we will generate both regional (promoter, gene body and CpG Island regions) as genome-wide methylation scores. For the genome wide analysis, a sliding window technique will be used to detect DMRs. The Chi-squared test will be used for statistical testing with either the False Discovery Rate (FDR) or Bonferroni correction for multiple testing. A FDR or Bonferroni adjusted p-value <0.05 will be considered significant. After DMRs are determined, Z-score transformation of the read count data will be applied for unsupervised hierarchical clustering analysis. Pathway analyses will be performed using <http://geneontology.org>.

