## 2. Objective(s)

1. Identify specific DMRs in first trimester residual NIPT samples related to adverse pregnancy outcome such as preeclampsia, intrauterine growth restriction and spontaneous preterm birth.
2. Identify underlying genes or genetic pathways related to identified DMRs, involved in disease development.
3. Create a validation cohort of DMRs in cfDNA for prospective subcohorts.

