##### 4.2 Inclusion criteria

In order to be eligible to participate in this study, a subject must meet all of the following criteria:

- Participated in the Predict study or delivered at the Erasmus MC Rotterdam.
- Participated in the TRIDENT-2 study during the same pregnancy and agreed with the use of residual material for research purposes.
- At least 18 years of age at the time of participating in above mentioned studies.
- Developed preeclampsia (n=20) or intrauterine growth restriction (n=20) or delivered spontaneously preterm (n=20) or had an uncomplicated pregnancy (n=20).

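### In sub-study 3, the sample search in section 5.1 reaches uncomplicated controls only through Predict, although 4.1 and 4.2 admit any Erasmus MC delivery, so source may be confounded with disease

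*Protocol*

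**What the plan says.** All sections cited are in sub-study 3 unless stated otherwise.

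- **Population (4.1).** Eligible women took part in TRIDENT-2 and "during the same pregnancy participated in the Predict study and/or delivered at the Erasmus MC Rotterdam".
- **Inclusion (4.2).** The source criterion is the same for every group: "Participated in the Predict study or delivered at the Erasmus MC Rotterdam". The group criterion is "Developed preeclampsia (n=20) or intrauterine growth restriction (n=20) or delivered spontaneously preterm (n=20) or had an uncomplicated pregnancy (n=20"), with no condition on plurality.
- **Exclusion (4.3).** No criterion is listed.
- **Search (5.1).** "Participation in the TRIDENT-2 study will be checked for Predict participants and for eligible patients who had complicated deliveries at the Erasmus MC Rotterdam", limited to the last two years.
- **Filling the groups (5.1).** "Cases and controls will be selected until twenty patients in each group are selected". No matching or balancing rule is given.
- **Timing.** The first objective (section 2) is to "Identify specific DMRs in first trimester residual NIPT samples related to adverse pregnancy outcome". The protocol summary adds that "NIPT sampling is usually performed between 11 and 13 weeks of gestation". That describes practice and is not an eligibility criterion.
- **Sample size (4.4).** Each group of twenty is split into ten for training and ten for internal validation.

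**The concern.** The four groups should differ in outcome and in as little else as the design can manage. Section 5.1 works against this. Cases can be found through Predict or through the hospital's delivery records, whereas an uncomplicated woman can be found only through Predict. Any characteristic that separates Predict participants from other women delivering at the hospital would then be partly aligned with case status.

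The protocol itself gives reasons to care. The introduction to Addendum 3 (sub-study 1) says that maternal factors such as obesity affect the amount of maternal cfDNA and hence the placental share. Section 1 of sub-study 2 puts that share at 13% on average, with a range of 3 to 30%. The analysis named in 5.1 is a Chi-squared test, which carries no covariates, so as the protocol stands protection has to come from selection.

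The second part concerns eligibility. With no exclusions and no singleton rule, a twin pregnancy or one with an abnormal NIPT result can enter a case group. Whether it could count as uncomplicated is not stated. Section 4.2 of sub-study 2 requires singletons for retrospective and prospective samples alike, so the omission here is a difference within the same programme.

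At stake is whether the reported DMRs reflect disease or reflect how the women were found.

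**Working it through.** **1. The plan's own figure.** Groups × (training + validation) = 4 × (10 + 10) = 80. This reproduces the stated total. The protocol states that no power calculation is possible, so there is none to reproduce.

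**2. Who can be found under each section.**

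| Woman | Eligible under 4.1 and 4.2 | Searched under 5.1 |
|---|---|---|
| Predict, complicated | yes | yes |
| Predict, uncomplicated | yes | yes |
| Erasmus MC only, complicated | yes | yes |
| Erasmus MC only, uncomplicated | yes | **no** |

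The sections disagree on the last row only, and that row decides where controls come from.

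**3. Size of the source imbalance.** Under 5.1 the non-Predict controls number 0 of 20. The non-Predict cases, k of 20, are not given, so the full range is shown. Fisher's exact test (two-sided) on k/20 against 0/20 serves only as a yardstick of imbalance:

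| k of 20 cases from outside Predict | p against 0 of 20 controls |
|---|---|
| 0 | 1.0 |
| 5 | 0.047 |
| 10 | 0.0004 |
| 20 | source and case status coincide |

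**4. Where in that range k might lie (illustration only).** Addendum 3 plans 300 women in thirty months and quotes 4–5% for pre-eclampsia. Residual samples cover two years (section 1), and NIPT uptake exceeded 40% in 2018 (section 1). Assume that Predict supplies women at the addendum's rate:

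- Women in two years: 300 / 30 × 24 = 240.
- Pre-eclampsia cases if all had NIPT: 240 × 0.04 to 240 × 0.05 = 9.6 to 12.
- At 40% uptake: 240 × 0.40 × 0.04 to 240 × 0.40 × 0.05 = 3.8 to 4.8.

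On these assumptions Predict yields about 4 to 12 of the 20 pre-eclampsia cases and leaves 8 to 16 to come from delivery records. At k = 8, the low end, Fisher p = 0.003. Higher Predict recruitment or incidence would shrink k, but nothing in the protocol secures that.

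**5. Can the internal validation detect it?** Training and validation patients come from the same twenty per group. If k = 10, a random split puts on average 5 of 10 non-Predict cases in each half, against 0 of 10 controls in each half. A source-driven DMR would therefore tend to replicate. The ten-sample rule in 4.4 is justified there as removing SNPs and other genomic variation. It does not address systematic differences between groups.

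**6. Plurality.** The documents give no share of multiples. For an assumed share q, the expected number in a group is 20q and P(at least one) = 1 − (1 − q)^20:

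| q | expected of 20 | P(at least one) |
|---|---|---|
| 1.5% | 0.3 | 0.26 |
| 3% | 0.6 | 0.46 |
| 10% | 2 | 0.88 |
| 20% | 4 | 0.99 |

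Each such pregnancy is 1 in 20 of a group and 1 in 10 of a training set. An unequal spread is possible, but its size cannot be derived.

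**7. Draw week.** No group-specific figure exists, so no difference can be computed.

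**The case against.** The strongest reply is that 5.1 is one descriptive sentence, while the summary, 4.1 and 4.2 use the same source wording for cases and controls. The team may well intend to take uncomplicated hospital deliveries too. That is fair, and it is why the point is a contradiction to reconcile and not a proven bias. But 5.1 is the operational instruction, and as worded it omits those women.

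The sources are also less separate than they look. Predict is a single-centre Rotterdam cohort, 4.1 allows overlap, and all plasma was taken for NIPT in TRIDENT-2 and is stored in one department. Nothing suggests that sample handling differs by source. What remains is a possible difference between the women themselves. Predict should not be read as a fertility cohort only, since Addendum 3 says it also studies pregnancy complications.

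This is also a declared pilot. In the planned prospective subcohort, cases and controls arise from the same 300 women, so a source artefact would not be expected to recur there. That limits the harm, but the NIPT study's own candidate list would still be affected.

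Three stronger readings are tempting, and the documents do not support them:

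- **That controls do differ in plurality and gestational age at draw.** The documents only leave these uncontrolled. Draw week is the weakest part: every group uses first-trimester NIPT material taken before the outcome, and no mechanism for a group difference is stated.
- **That source confounding could never be undone.** Predict is searched for cases as well, so a Predict-only comparison is possible for whatever cases it yields. On the illustration above that could be as few as 4 pre-eclampsia cases, below the ten that 4.4 treats as the minimum for a stable DMR count.
- **That multi-factor matching and model covariates are required.** Their merit is debatable, covariates do not fit the stated Chi-squared test, and adjustment may sit in an analysis plan not shown.

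**Conclusion.** The point holds in limited form. Section 5.1 contradicts 4.1 and 4.2 on where controls may come from. If 5.1 is followed, all 20 controls are Predict participants, while each case group may contain anywhere from 0 to 20 women from outside Predict. Source may then be confounded with disease, to an extent the documents do not give, and the internal validation set cannot reveal it.

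The estimate of 8 to 16 non-Predict pre-eclampsia cases rests on the assumed Predict recruitment rate, the quoted incidence and NIPT uptake between 40% and 100%. It is illustrative. The conclusion needs only the wording of 5.1.

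The absence of exclusions and of a singleton rule adds a possible imbalance in multiple or chromosomally abnormal pregnancies, also of unknown size. For draw week, the supportable statement is that the intended window is not a criterion. The documents do not show that the groups differ on it.

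Sampling frame and eligibility are fixed in this protocol, so the correction belongs here and should precede sample retrieval.

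**What to change.** - **Section 5.1.** Reconcile it with 4.1 and 4.2: also search uncomplicated Erasmus MC deliveries of the same two years, and draw controls from the two sources in about the same proportion as cases.
- **Section 4.3.** List as exclusions multiple pregnancy, and abnormal NIPT or known fetal chromosomal or congenital anomaly, for all four groups.
- **Section 4.2.** Make the first-trimester draw window an eligibility criterion, and report a check that draw week is similar across groups.
- **Optional.** Add a sensitivity comparison restricted to Predict cases and Predict controls, with the number of cases it rests on.

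The cost is one extra records query and a few otherwise eligible women passed over, from a sample store that covers about two years. The total stays at 80.
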